**Number of subjects**

Reilly reported that outbreak of gene concerned with platelet which could increase risk of MI occurred at 3-6 days after operation in patients who received continuously aspirin until operating day before coronary artery bypass surgery. In the study, GPIIb, GpIIIa, COX-1 gene expression increased by 3 times in all of 11 patients compared to baseline. For OPCAB, there was no data on GpIIb, GpIIIa, COX-1 gene expression. Therefore, 20 subjects are needed for each group, that is, total of 40 subjects are needed for this study. Considering the loss rate of 20%, total of 48 subjects will be needed.

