**Laboratory evaluation lists**

At the time points (T1, T2, T3, T4, T5, T6, T7)

- Platelet count

- Conventional coagulation tests (CCT : INR, aPTT, fibrinogen)

- Activated clotting time (ACT)

- Capillary closure time (PFA-100/EPI, PFA-100/ADP)

- D-dimer

- von Willebrand factor

- Rotational thromboelastometry (ROTEM)

- Platelet function (Verify/Now accumetrics)

- Platelet aggregation (multiplate , inducer : collagen, ADP, TRAP-6, arachidonic acid)

- Annexin V (flow cytometry)

- platelet P-selectin (flow cytometry)

- platelet CD41(flow cytometry)

- PAC-1 (flow cytometry)

- platelet CD63( flow cytometry)

- Thromboxan B2

At the time points (T1, T6)

- GPllb, GPllla, COX-1 mRNA (RT-PCR)

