**Statistical analyses**

Statistical analyses will be performed with intention-to-treat.

If data will be normal distributed, we will use student t-test or Chi square test. Otherwise, Mann-Whitney test or Fisher’s exact test will be used.

For the primary outcome, increase of GPIIb mRNA, independent t-test will be used.

For the evaluation discrepancy of platelet mRNA expression by aspirin effect between two groups at each time points, we will use the generalized estimating equation/general linear model. P-value < 0.05 will be considered to be significant.

Repeated-measures analysis and Bonferroni correction will be used for adequate analysis between groups.

Data will be presented as mean ± Standard deviation, median [interquartile range], and number of patients (%). All statistical analyses will be performed with IBM SPSS Statistics software (version 21, SPSS Inc., IBM Corporation, USA).

References

1. Bernard Lo, Rob Fijnheer, Domenico Castigliego, Cornelius Borst, Cor J. Kalkman, Arno P. Nierich, Activation of hemostasis after coronary artery bypass grafting with or without cardiopulmonary bypass. Anesth Analg 2004; 99: 634-40

2. Alessandro Parolari, Luciana Mussoni, Marta Frigerio, Moreno Naliato et al., The role of tissue factor and P-selectin in the procoagulant response that occurs in the first month after on-pump and off-pump coronary artery bypass grafting. The journal of thoracic and cardiovascular surgery 2005; 130(6): 1561-1566

3. Raymond Cartier, Current trends and technique in OPCAB surgery. J Card Surg 2003; 18: 32-46

4. Frantisek Bendar, Pavel Osmancik, Tomas Vanek, Heidi Mocikova, Martin Jares, Zbynek Straka, Petr Widmsky , Platelet activity and aspirin efficacy after off-pump compared with on-pump coronary artery bypass surgery: results from the prospective randomized trial PRAGUE 11-Coronary Artery Bypass and Reactivity of Thrombocytes (CABARET). The journal of thoracic and cardiovascular surgery 2008; 136(4): 1054-1060

5. Robert Poston, Junyan Gu, James Brown, James Gammie, Charles White, Jeffrey Manchio, Richard N. Pierson et al., Hypercoagulability affecting early vein graft patency dose not exist after off-pump coronary artery bypass. J of cardiothoracic and vascular anesthesia 2005; 19(1): 11-18

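### Bonferroni for the repeated between-group comparisons is valid, but Holm gives the same error guarantee with equal or better power; the many markers are best labelled exploratory

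*Protocol*

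**What the plan says.** The Statistical analyses section of the protocol gives the primary outcome a test of its own: "For the primary outcome, increase of GPIIb mRNA, independent t-test will be used". It then names a generalized estimating equation or general linear model for "platelet mRNA expression by aspirin effect between two groups at each time points", sets the criterion "P-value < 0.05 will be considered to be significant", and adds the multiplicity sentence: "Repeated-measures analysis and Bonferroni correction will be used for adequate analysis between groups". It does not say which tests the Bonferroni correction spans.

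The Laboratory evaluation lists section sets the volume of comparisons. The coagulation and platelet markers are taken "At the time points (T1, T2, T3, T4, T5, T6, T7)". One line alone holds four measures: "Platelet aggregation (multiplate , inducer : collagen, ADP, TRAP-6, arachidonic acid)". The three genes are measured only "At the time points (T1, T6)".

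The Number of subjects section says: "Therefore, 20 subjects are needed for each group, that is, total of 40 subjects are needed for this study". It raises this to 48 for a 20% loss and gives no effect size, standard deviation or power.

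**The concern.** The protocol commits to one correction method, and a better one is available for the same p-values. Bonferroni holds every one of seven comparisons to the strictest threshold, even after some have been rejected. Holm relaxes the threshold after each rejection and keeps the same guarantee. In a trial with about 20 patients per arm, real differences at some times may be missed that Holm would have declared.

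A second matter is related but separate. If the correction works within a marker, it does not limit the error across all markers to 5%. A reader of the trial report could take an isolated significant marker as confirmed when it is one of many that were tested.

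Only the reading of the secondary laboratory markers is at stake. The primary comparison is one test on one gene and needs no correction.

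**Working it through.** **The plan's own figures.** The protocol states no adjusted alpha and no power for these comparisons, so there is nothing to reproduce on this point. The sample size steps are 20 × 2 = 40 and 40 × 1.2 = 48. After a 20% loss, 48 × 0.8 = 38.4 remain, or about 19 per arm. The base of 20 per arm cannot be reproduced.

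**Inputs from the protocol.** Alpha is 0.05 (two-sided assumed, since sidedness is not stated), there are seven time points T1 to T7, and allocation is 1:1. Counting the list gives: platelet count 1; INR, aPTT and fibrinogen 3; ACT 1; PFA-100 2; D-dimer 1; von Willebrand factor 1; ROTEM 1; VerifyNow 1; Multiplate 4; flow cytometry 5; thromboxane B2 1. The total is 21 markers with ROTEM counted as one, hence 21 × 7 = 147 comparisons.

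**Assumptions.** The Bonferroni family is the seven times within one marker. Where a difference exists it is 0.9 SD. The times are equally correlated within a patient.

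**Thresholds.** Bonferroni compares every p-value with 0.05/7 = 0.00714. Holm orders the p-values and compares the k-th smallest with 0.05/(8 − k), stopping at the first failure: 0.00714, 0.00833, 0.0100, 0.0125, 0.0167, 0.0250, 0.0500. No Holm threshold lies below 0.00714, so every Bonferroni rejection is also a Holm rejection. The first threshold is the same, so the chance of at least one rejection is identical.

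**Error within one marker when no time differs** (simulation, 20 per arm, 40,000 trials); Bonferroni and Holm give the same values:

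| Correlation between times | 0 | 0.5 | 0.7 | 0.9 |
|---|---|---|---|---|
| Family-wise error | 4.8% | 4.1% | 3.2% | 2.1% |

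**Power at one time point, 19 per arm.** The noncentrality is 0.9 × √(19/2) = 2.77 on 36 degrees of freedom. Two-sided t-test power is 77% at 0.05, 48% at 0.00714 and 15% at 0.05/147 = 0.00034.

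**Average power per truly different time point, 19 per arm** (simulation, correlation 0.3 to 0.8):

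| Times that truly differ | Bonferroni | Holm |
|---|---|---|
| 1 of 7 | 48% | 48% |
| 4 of 7 | 48% | 52% |
| 7 of 7 | 48% | about 58% |

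At 20 per arm and correlation 0 to 0.9 the pattern is the same: 51% to 51% with one time, 51% to 53% with three, and 50–51% to 60–63% with all seven.

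**Error across markers with the correction within each marker.**
- Expected false positives over 147 null tests: 147 × 0.05 = 7.35 uncorrected; 147 × 0.05/7 = 1.05 with Bonferroni.
- Chance of at least one, all tests independent: 1 − 0.95^147 = 0.9995 uncorrected; 1 − (1 − 0.05/7)^147 = 0.65 with Bonferroni.
- Allowing for correlation between times but independent markers: 1 − (1 − 0.032)^21 ≈ 0.50 at correlation 0.7; 1 − (1 − 0.021)^21 ≈ 0.36 at 0.9. Correlation between markers lowers these further.
- When no marker differs, Holm within each marker gives the same values as Bonferroni.

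**The case against.** The strongest reply is that nothing here is wrong. Bonferroni controls the family-wise error under any dependence, and a conservative correction for secondary laboratory markers is a legitimate choice. The gain from Holm is nil with one differing time and about four percentage points with four of seven; it reaches about ten only if all seven differ. Every power figure rests on an effect the protocol does not give. The family of tests is a detail commonly left to the statistical analysis plan, which is not shown. All of this stands, and it limits the point to an optional improvement. It does not remove the point: the protocol names a specific method, and Holm is never worse at any effect size or correlation.

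A reader might infer more than the documents support:
- **That Bonferroni is the weakest valid correction.** It is conservative, but other valid procedures, such as Scheffé's, can be weaker.
- **That the protocol applies it marker by marker.** That is an assumption made here for the calculation.
- **That it does nothing across the 21 markers.** Within-marker correction still cuts the expected false positives from 7.35 to 1.05.
- **That Holm would repair the error across markers.** With no true differences it leaves that error where Bonferroni leaves it.
- **That the three genes carry an uncontrolled error of 1 − 0.95³ = 14%.** GPIIb is the sole primary outcome with its own t-test, and the protocol makes no joint claim for the three genes. The genes are measured at two times, so the seven-time calculation does not describe them.

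**Conclusion.** The point holds as a small, inexpensive improvement to the secondary comparisons, not as an error in the plan. Replacing Bonferroni with Holm keeps the same family-wise guarantee and adds between nothing and about ten percentage points of power per truly different time point. Those figures assume a family of seven times within a marker, 19 per arm, a 0.9 SD difference and equal correlation between times. That Holm is never worse needs none of these assumptions.

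The error across about 21 markers, up to about 65% under independence, is a matter of interpretation that neither method settles when used within a marker. It is no breach of a promise, since the protocol claims no error control across markers. Correcting over all 147 comparisons would hold 5% but leave about 15% power at the same assumed effect, so labelling the markers exploratory is the better answer.

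**What to change.** In the Statistical analyses section, replace the Bonferroni correction with the Holm step-down procedure for the between-group comparisons at each time point within each marker measured at T1 to T7, and state that the family is the seven times of one marker. Add that these markers are exploratory and that no error control is claimed across them.

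Leave the GPIIb t-test and the sample size as they are. The cost is a change of wording and a simple step-down on p-values that the analysis produces anyway, with no new data or patients. The one drawback is that Holm has no simple matching confidence intervals, whereas Bonferroni has them at level 1 − 0.05/7, about 99.3%. If intervals are wanted, they can be reported unadjusted and described as such.
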